### Statistical analysis

We will generate descriptive statistics for participants’ demographics, lifestyle behaviors (physical activity, tobacco use), family history of chronic disease, history of other comorbidities (e.g., hypertension, diabetes, dyslipidemia, thyroid disease), and cancer treatment-related exposures. We will assess participation bias by comparing demographics (age, gender, race/ethnicity) and treatment-related exposures among participants and non-participants. Although the number of adverse events is not the major outcome of the study, we will report any adverse events during the study intervention period. We will use a two-sided type I error=0.05. An intention-to-treat analysis will be done by including all randomized participants. We will also conduct another analysis by excluding participants that demonstrate <70% compliance rates within the telehealth exercise sessions completed (17/24). *Hypothesis 1*: The intervention will improve the SPPB test, as objectively measured using Bluetooth-enabled biosensors. We will assess changes in physical function from baseline to week 9 by using the Generalized Estimation Equation (GEE) model with an indicator variable of time, accounting for within-person correlations in measurements. Treatment by time interaction will be included in GEE and its significance tested to assess treatment effects. Body mass index, age, and race will be determined through medical records and included in GEE as a priori covariates for adjustment. Changes in physical function measures from baseline to week 9 will also be examined by a paired *t*-test (within the treatment group). A 2-sided significance level of *p*<0.05 will be used. *Hypothesis 2*: The intervention will improve a 5-scale frailty index, as measured by patient-reported questionnaires. We will assess group differences in changes in the proportion of participants who are of pre-frail or frail from baseline to week 9 using the GEE approach for proportions, accounting for correlation between measurements. As in hypothesis 1, we will include the same covariates for adjustment in the analysis. *Hypothesis 3*: Intervention-related improvements in physical function and frailty will be sustained at week 17. We will examine the long-term effects of the telehealth exercise intervention by fitting GEE models for the outcomes at weeks 9 and 17. The model will include the treatment main effect (to allow for group differences at week 17), time, and the treatment group by time interaction. Contrasts will be used to test if the group difference at week 17 equals that at week 9. As in hypothesis 1, we will include the same covariates for adjustment. Additionally, between-group differences in outcome values at week 17 will be computed, along with 95% confidence intervals, and compared to the differences at week 9. Linear mixed-effects modeling will be used to evaluate the effect of interventions over time on the primary and key secondary outcomes. The models incorporate subject-specific random effects to account for within-subject correlation due to repeated measures. Group averages, as well as subject-specific intercepts and slopes, will be estimated to capture potential variations in the baseline values and slopes among individuals. Linear mixed-effects models accommodate missing data due to dropout, such that all randomized participants can be included. We will compare participants who complete the study with those who do not and identify potential factors that are associated with dropout. An interim analysis is not currently planned for this study.

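### Hypothesis 3 makes sustained benefit the null of its only named test, attaches no criterion to the week-17 interval, and leaves baseline SPPB out of its GEE model

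*Protocol article*

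**What the plan says.** All of this is in the Statistical analysis section of the protocol article.

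- Hypothesis: "Intervention-related improvements in physical function and frailty will be sustained at week 17".
- Data: the long-term effect is examined "by fitting GEE models for the outcomes at weeks 9 and 17".
- Terms: "The model will include the treatment main effect (to allow for group differences at week 17), time, and the treatment group by time interaction". The Hypothesis 1 covariates are carried over: "Body mass index, age, and race will be determined through medical records and included in GEE as a priori covariates for adjustment". Baseline SPPB is in neither list.
- Test: "Contrasts will be used to test if the group difference at week 17 equals that at week 9".
- Estimation: "between-group differences in outcome values at week 17 will be computed, along with 95% confidence intervals, and compared to the differences at week 9". No margin, retained fraction or decision rule accompanies this.
- Error rate: "We will use a two-sided type I error=0.05".

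The same section later plans linear mixed-effects models of the intervention effect over time for the primary and key secondary outcomes, with subject-specific intercepts and slopes. It does not link the Hypothesis 3 contrast or the week-17 difference to those models. The Power calculations section covers week 9 only.

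**The concern.** Sustainability is part of the study's stated purpose (Abstract, Background). The claim to be supported is that benefit persists, and the only test named has no change since week 9 as its null. A significant result can count against the claim. A non-significant one is only absence of evidence, and it becomes more likely as the trial gets smaller, noisier or loses more patients. If it were read as support, a stated aim could be declared met because the trial is small.

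The week-17 group difference with its confidence interval is the quantity that can show whether benefit is still present. In the Hypothesis 3 model it is estimated without the baseline value, although the article expects strong within-person correlation.

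**Working it through.** **Inputs from the article.** 30 per arm randomised. Attrition is 20% to week 9 (Power calculations) and 20% to week 17 (Discussion), so 30 × 0.8 = 24 per arm. SD 2.7, target difference 1 point, and correlations of 0.8 or more, 0.70, and 0.9 from the earlier study (Power calculations). Two-sided alpha 0.05.

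**Assumptions.** The article gives no correlation between weeks 9 and 17 or between baseline and week 17. I take 0.7, 0.8 and 0.9, and SD 2.7 at every visit. Half loss means 0.5 point and full loss 1 point.

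**The plan's own figure.** No power is stated for Hypothesis 3. For week 9, the 1-point claim reproduces: SD 2.7, r = 0.9 and 24 per arm give 82% power on change scores. The 80% power at effect size 0.40 does not: with r = 0.8 and 24 per arm I get 59% on change scores and 64% with baseline as a covariate. That is a separate matter, and nothing below depends on it.

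**1. The equality contrast.** The week-17 difference minus the week-9 difference compares the arms on change between those visits:

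SE = 2.7 × √(2(1 − r) × 2/24)

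At r = 0.8, SE = 2.7 × √(0.4 × 2/24) = 0.493. For half loss, 0.5/0.493 = 1.01, and P(non-significant) = 1 − Φ(1.01 − 1.96) − Φ(−1.01 − 1.96) ≈ 0.83.

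Where two figures appear, they are the normal approximation and the noncentral t:

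| r | SE | Half lost: non-significant | All lost: non-significant |
|---|---|---|---|
| 0.7 | 0.604 | 87% | 62–63% |
| 0.8 | 0.493 | 83% | 47–49% |
| 0.9 | 0.349 | 70–71% | 18–20% |

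With all 30 per arm retained, the half-loss figures are 85%, 80% and 65% (noncentral t).

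**2. Baseline and the contrast.** With equal correlations between visits, Cov(Y0, Y17 − Y9) = σ²(r − r) = 0. Adding baseline gives the contrast essentially nothing.

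**3. Baseline and the week-17 difference.** Without baseline, the 95% half-width is 1.96 × 2.7 × √(2/24) = 1.53 points. With baseline as a covariate, multiply by √(1 − r²):

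| r | Half-width with baseline | Power for a true 1-point difference at week 17 |
|---|---|---|
| 0.7 | 1.09 | 44% |
| 0.8 | 0.92 | 57% |
| 0.9 | 0.67 | 84% |

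Without baseline that power is 25%. The 1.53 is before adjustment for BMI, age and race, whose effect cannot be computed from the article.

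**4. What confirming retention would need.** Take an illustrative margin of 0.5 point, no true loss, one-sided 0.025 and 80% power. Then n per arm = 2 × 2.7² × 2(1 − r) × (1.96 + 0.84)²/0.5² = 275, 184 or 92 analysed at r = 0.7, 0.8 or 0.9. Dividing by 0.8 gives 344, 230 or 115 randomised per arm, against 30 planned.

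**The case against.** - **No stated decision rule.** A reader might infer that the plan will declare benefit sustained whenever the contrast is non-significant. The article does not say so. It also commits to week-17 differences with 95% intervals, which is much of what is needed, and the threshold could sit in an analysis plan that is not shown. This stands as a limit on the point. What remains is that the article does fix the test, its data and its terms, and the test is one that cannot support the hypothesis.
- **Complete loss.** A reader might also infer that the contrast would usually miss a benefit that has vanished. That holds at r = 0.7, but not at 0.8 (47–49%) or 0.9 (18–20%). For half loss, *usually* holds across 0.7 to 0.9, but not if the correlation exceeds about 0.95, nor generally if the week-9 benefit is larger: for 2 points, half loss is non-significant about 20–63% of the time.
- **No benefit at either visit.** Equality would then hold too. This is largely answered, because Hypothesis 3 concerns improvements that Hypothesis 1 tests at week 9.
- **The mixed model.** If baseline is a response in it, which is the natural reading though not explicit, the week-17 difference in change from baseline has a half-width of about 0.97 at r = 0.8, close to the 0.92 above. So 1.53 describes the Hypothesis 3 GEE only. It still matters, because Hypothesis 3 is tied to that GEE.
- **The replacement is not a retention test.** An interval excluding zero at week 17 shows some benefit remaining, not that the week-9 benefit was kept. A fully sustained 1-point benefit would miss that criterion 43% of the time at r = 0.8. This is correct, and the fix has to say so.

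**Conclusion.** The point holds in limited form. Hypothesis 3 is paired with an equality test whose non-rejection is not evidence for it, and no other criterion is given. If half of a 1-point benefit were lost, that test would be non-significant in about 71–87% of trials of this size, and if all were lost in about 20–62%. Separately, omitting baseline SPPB from the Hypothesis 3 GEE leaves a week-17 half-width of about 1.53 points where 0.67–1.09 is attainable. The omission is not a flaw in the equality contrast itself.

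These sizes rest on SD 2.7 at each visit, 24 per arm, a 1-point week-9 effect and correlations of 0.7–0.9 that the article does not give for the visits concerned. They apply to SPPB. The frailty proportions were not computed, because no rates are given. This should be fixed before the data are analysed, but it does not touch the primary week-9 analysis.

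**What to change.** 1. Estimate the week-9 and week-17 group differences from one model that includes baseline SPPB, either as a covariate or as a response with the arms constrained equal at baseline.
2. Base the claim that benefit is still present at week 17 on the baseline-adjusted week-17 difference and its 95% confidence interval.
3. Report the week-17 minus week-9 contrast with its 95% confidence interval as the amount of benefit retained or lost.
4. State that a non-significant contrast is not evidence of sustainability, and that the trial is not sized to confirm full retention.

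The cost is wording in the analysis section. Baseline SPPB is already collected at week 0, and no patients, visits or procedures are added.

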
## Discussion

This study will address current knowledge gaps by including an objective assessment of physical function and frailty before and after a telehealth exercise intervention in patients with multiple myeloma. Physical function and frailty have emerged in recent clinical and epidemiological investigations as intervention targets to improve in hematological cancer survivorship [30–32]. To date, controlled exercise trials in cancer populations have primarily targeted survivors of solid malignancies such as breast [33–35], prostate [36–38], colorectal [39–41], and lung [42–44] cancer. There is a paucity of information on optimal rehabilitation strategies to improve physical function and frailty in patients with multiple myeloma at risk of developing frailty. Moreover, the efficacy and sustainability of fully remote exercise interventions have not been evaluated in this population. The current study presents a unique opportunity to determine the efficacy and sustainability of a telehealth exercise intervention on physical function and frailty in patients with multiple myeloma who have undergone autologous HSCT, which is currently a rapidly growing population at high risk for comorbidities.

Although this study will provide the first evidence of a novel telehealth exercise approach targeting frailty and physical function in patients with multiple myeloma, it is beyond the scope of the current study to elucidate the mechanisms of improving frailty with exercise. Our study has the potential to demonstrate that frailty is maintained and not worsened during the intervention when compared to the delayed control group, which will be a clinically important finding. We recognize that poor retention is a possibility, given the time and effort needed to partake in an intervention study. Therefore, we have accounted for a 20% attrition rate (from randomization to week 17 post-intervention). This takes into consideration patient death, recurrence of cancer, illness, or loss to follow-up. We acknowledge that there may be differential loss to follow-up according to participant attributes and prognosis, which may contribute to participation bias and/or survival bias. To minimize participation bias, we will incorporate many of the strategies (e.g., reminders, incentives) that we have successfully used to maintain excellent participation rates in our exercise intervention studies to date. Attrition will be monitored in real time, allowing us to address obstacles in a timely manner. Differential loss to follow-up due to prognosis, death, and missing data will be addressed using statistical methods of pattern mixture models and multiple imputation. Finally, recruitment of patients with multiple myeloma can be challenging. However, our ongoing successful recruitment strategies in place for the current study, which includes collaborating with the hematology team at COH, appear to be a successful recruitment plan.

This study will provide critical evidence that contributes to the development of comprehensive telehealth exercise programs in HSCT survivors by investigating the effects of an 8-week telehealth exercise intervention in HSCT survivors with the potential of demonstrating improvements and sustainability in physical function. If successful, our approach would be low cost, easily disseminated, and have potential implications for the management and prevention of frailty in HSCT survivors as well as other cancer survivors at risk of developing frailty after cancer treatment.

### Trial status

Protocol version number and date: #211981 (September 29th, 2021), date of first recruitment: October 4, 2021, approximate date to complete recruitment: June 30th, 2023

## Data Availability

The datasets used and/or analyzed during the current study are available from the corresponding author on reasonable request

## Abbreviations

COH: City of Hope
FACT-MM: Functional Assessment of Cancer Therapy – Multiple Myeloma
HSCT: Hematopoietic stem cell transplantation
SPPB: Short Physical Performance Battery
GEE: Generalized Estimation Equation
